## Abstract

Advice to stay active is the primary management strategy for sciatica. Other conservative treatments such as neural management techniques may also contribute to sciatica recovery, but currently, the effects have not been robustly assessed. Thus, the aim of this study is to compare the effects of adding neural management to advice to stay active versus advice to stay active alone in improving pain intensity and functional limitation. Secondarily, to compare the effects of the experimental intervention in the sciatic neurodynamic, pain modulation, and psychosocial factors. A parallel-group, controlled, examiner-blinded superiority clinical trial randomised at a 1:1 allocation will be conducted in 210 participants with chronic sciatica. Patients will be recruited from outpatient physiotherapy clinics and community advertisements. The experimental group will receive neural mobilisation techniques and soft tissue mobilisation techniques for 30 minutes per session, 10 weekly sessions, plus advice to stay active on their activities of daily living, information on physical activity, imaging tests, and sciatica for 5 biweekly sessions lasting 25–30 minutes. The control group will receive advice to stay active only. The re-evaluation will be performed out after 5 weeks, 10 weeks, and 26 weeks after randomisation and primary endpoints will be pain intensity and functional limitation at 10 weeks. Secondary outcomes will include neuropathic symptoms, sciatic neurodynamic, pain modulation, and psychosocial factors. Adverse events and patient satisfaction will be assessed. Ethical approval has been granted from an Institutional Human Research Ethics Committee.

**Trial registration**: Trial was prospectively registered in the Brazilian Registry of Clinical Trials (number: RBR-3db643c).

## Introduction

Low back pain (LBP) is the leading cause of years lived with disability worldwide [1]. Patients with chronic LBP usually present co-occurring pain [2]. In primary care, the prevalence of patients with back-related leg pain varied from 48% to 74% depending on the used description [3]. Sciatica is also known as lumbosacral radiculopathy that presents as a severe form of LBP characterised by radiating leg pain and is considered chronic when symptoms last more than 12 weeks [4]. Patients with sciatica have a worse prognosis, higher incidence of disability compensation, greater pain intensity and functional limitations compared to patients with localised LBP [5–8]. The success of the treatment is dependent on various identified prognostic factors such as sociodemographic (e.g. male), clinical (e.g. longer duration of LBP, comorbidities), lifestyle (e.g. smoker), and psychosocial factors (e.g. kinesiophobia) [9]. These prognostic factors are important considerations to identify appropriate treatment and management of patients with sciatica.

The treatment of sciatica is challenging. Although treatment should be patient-centred and aligned with clinical practice guidelines, local pathways can make it difficult for patients to achieve proactive capability to manage their sciatica [10]. Clinical practice guidelines and systematic reviews recommend several conservative treatments as the initial treatment for patients with sciatica [11–13]. Referring acute sciatica patients to physical therapy improve clinical outcomes [14]. Conservative treatment strategies aim to reduce pain intensity and maintain function. There is evidence that active conservative treatment is effective in patients with severe sciatica [12, 15], and advice to stay active continues to be a first-line recommendation for the management of sciatica in most international clinical practice guidelines [13, 16]. Other conservative strategies, such as exercise, has been found not to be superior to advice to stay active in reducing pain intensity and disability of people with sciatica [17]. However, neurodynamic treatment has shown a significant reduction of leg pain intensity and improved function after four weeks of intervention in patients with chronic nerve-related leg pain, although there was no differences between interventions on the primary outcome after two weeks [18].

There is growing evidence that neural management may facilitate recovery in patients with sciatica. Neural management aims to restore peripheral nervous system homeostasis through nerve and surrounding tissue mobilisation [19, 20]. Neural management may assist in the restoration of the neurodynamic of the sciatic nerve. Compression of the sciatic nerve may be associated with changes in nerve function [4]. Besides, the improvement of clinical symptoms in sciatica patients is related to the normalisation of nerve mobility [21]. A decrease in intraneural oedema and improvement in temporal summation and median nerve latency were presented after neural management for different conditions (e.g. nerve-related neck and arm pain, tarsal tunnel syndrome, and plantar heel pain) [22]. Neural involvement may be investigated by ultrasound imaging. The use of ultrasound images to assess the properties of nerves is becoming increasingly popular [23]. Ultrasound images quantify the nerve neurodynamic, including excursion and the cross-sectional area of the nerve [24–26]. Thus, ultrasound images represent a resource able to assess the effect of neural management treatment on nerve structure.

The benefits of neural management as a treatment strategy in patients with chronic sciatica is currently limited by low-quality evidence. Neural management has shown positive results for improving pain and function in patients with LBP [22, 27, 28] and to be superior to other treatments of exercise, conventional physiotherapy, traction or manual therapy for patients with chronic nerve-related musculoskeletal pain such as sciatica, chronic radicular LBP, nerve-related neck and arm pain, and carpal tunnel syndrome [29]. Previous studies using neurodynamic treatment presented methodological limitations as high population heterogeneity [27] and small sample size [18, 28]. Despite being a frequently used strategy, there is a lack of good methodological studies to demonstrate the clinical effects and benefits of neural management for patients with chronic sciatica. Therefore, we propose a randomised controlled clinical trial to analyse the effects of adding neural management to advice to stay active versus advice to stay active alone in medium-term (10 weeks) improvement of pain and function limitation for patients with chronic sciatica. Secondarily, the study will compare the effects of adding neural management to advice to stay active versus advice to stay active alone in the neuropathic symptoms, sciatic neurodynamic, pain modulation, and psychosocial factors.

## Materials and methods

### Study design

A two-armed, randomised, controlled, examiner-blinded, superiority clinical trial. The study will be conducted according to the requirements Consolidated Standards of Reporting Trials (CONSORT) [30] and Standard Protocol Items: Recommendations for Interventional Trials (SPIRIT) (S1 File) [31].

### Registry

This trial was approved by the Research Ethics Committee of Augusto Motta University Centre (number: 40500720.8.0000.5235), in accordance with the Helsinki Declaration for research in humans and was prospectively registered in the Brazilian Registry of Clinical Trials (number: RBR-3db643c).

### Setting

The trial will be conducted in the Augusto Motta University Centre outpatient physiotherapy, located in Rio de Janeiro, Brazil.

### Recruitment

Participants will be recruited when they seek the outpatient physiotherapy due to chronic sciatica and by community adverts in the local population. Potential participants could be screened by phone to determine eligibility before the assessment session. All patients who met the eligibility criteria will sign the informed consent form at the recruitment process.

### Eligibility criteria

Potential participants will be assessed by a physiotherapist ([name]) to confirm the diagnosis of sciatica. We will include adults (18–65 years old) with chronic sciatica with moderate or severe leg pain intensity (greater than 3 on the Numerical Pain Rating Scale) [32, 33]. Sciatica will be defined as pain radiating unilaterally to the lower limb below the knee, with symptoms of paraesthesia along the path of the sciatic nerve, involving the dermatomes of L4 to S1, in addition to possible neurological symptoms persistent or recurrent for more than three months [4, 7, 34]. The inclusion criteria will also include the presence of higher pain intensity in the lower limb compared to the lumbar region, being symptomatic at the time of assessment, and clinical evaluation to confirm the diagnosis of chronic sciatica. The clinical diagnosis will be confirmed if the participant has two or more positive findings based on 5 items: positive neural tension of the sciatic nerve, neurologic deficit, pain below the knee, pain intensity higher in the lower limb compared to the lumbar region, and subjective sensorial changes [33].

The participants will be excluded if they are already in treatment due to sciatica or planning to undergo any other procedures for sciatica treatment in the study period, present known or signs of serious spinal pathology (i.e., cauda equine syndrome, trauma, fractures, or cancer); history of abdominal, lumbar, or lower limb surgery in the past year; rheumatologic disease in the acute inflammatory phase; if they are receiving disability compensation due to LBP; pregnant or puerperal women; self-reported psychiatric diagnosis; and history of cancer or cancer-related pain.

### Recruitment and enrolment strategies

Participants will be recruited from outpatient physiotherapy clinics. We will use different recruitment methods, including physiotherapist referrals who assist the patients in outpatient physiotherapy, community adverts in the local population, and internet adverts. All participants will receive a flier explanatory about the advantage, rights, duties and responsibilities of the participants included in the research. Participants will be recruit continuously until the desired sample size is reached.

### Randomisation, allocation, and blinding procedures

After the initial assessment, participants will be randomised to one of two groups; neural management plus advice versus advice alone (1:1 allocation). The allocation sequence will be prepared a priori using the "Research Randomizer", an online random number generator available at https://www.randomizer.org/. The randomisation of the participants will be performed using randomly permuted blocks of 4 and 6.

An independent examiner not involved in the study recruitment, assessment, or data analysis will allocate participants to the randomised group to ensure secret allocation from participants. Concealed allocation will be granted using numbered, sequentially ordered, sealed opaque envelopes with an index card written in which intervention group the participant will be enrolled. The envelopes will be numbered consecutively. The same examiner will open the sealed envelopes after the informed consent form has been completed, and the participant carries out the initial assessment. The participants will receive a unique study enrolment number and be referred to the physiotherapist responsible for the intervention group in which the participant was allocated.

Subsequently, the interventions will be performed by the physiotherapist’s authors ([name] and [name]) at the outpatient physiotherapy. The physiotherapists will be blinded to the initial assessment. The physiotherapist ([name]) responsible for assessing pre-treatment, during, and post-treatment will be unaware of randomisation and be blinded to treatment allocation. Statistical analysis will also be conducted blinded to group allocation. Due to the nature of the interventions, physiotherapists and participants will not be blind to treatment allocation. To guarantee that the treatment expectation is evenly balanced between the groups, the participants will not know the study hypothesis. The unblinding of the study will occur in case any serious adverse event occurs or once the completion of the research and the data analysed and interpreted.

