### Adherence to interventions, adverse events, and assessment of patient satisfaction

Adherence to home treatment will be assessed through the activity’s agenda, in which participants must register the activities that were performed at home in the days between the sessions, in order to remain active. High adherence will be defined as ≥ 70% attendance at sessions [68].

Serious adverse events and adverse events that occurred during the intervention will be assessed by a self-reported questionnaire developed by the researchers to register the symptom and/or adverse event, with duration and intensity details. Serious adverse events will include any significant disability, hospitalisation, life-threatening, and death, and will be reported immediately to the researchers and ethics committee.

Patient satisfaction assessment will be performed through MedRisk, a questionnaire capable of measuring the level of satisfaction of the patient who will be receiving interventions through physiotherapists. MedRisk consists of 20 items, 10 items related to the therapist-patient interaction, 2 items that are considered global and 8 items that evaluate other domains. Participants will score patient satisfaction using a Likert scale ranging from 1 (strongly disagree) to 5 (strongly agree). The higher the score, the higher the satisfaction [69].

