### Data collection and management

Patient’s characteristics at baseline assessment will be collected immediately before randomisation. All the data collected, and outcomes will be obtained using printed questionnaires. The original data will be scanned as image files by a research assistant and shared with a second research assistant. Data integrity will be audited by regularly scrutinising data for omissions and errors by double entered with automated checks in Microsoft Excel spreadsheet (Microsoft Corporation) performed by [name] remotely. Discrepancies will be explored and resolved by checking the original data.

Participants will be identified by an individual trial number to ensure confidentiality, and confidentiality regarding the data collected in all stages will be guaranteed by stored on password-protected servers. The paper-form data will be stored in locked filing cabinets at the Postgraduate Program in Rehabilitation Sciences. Data will only be accessible to the research team. All statistical analyses will be performed using the individual number of each participant and the statistician will be blinded to the group. The results will be presented by group data and any individual data will be spread to ensure confidentiality is preserved.

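### As written, one serious adverse event in any participant unblinds the whole study, which conflicts with the commitments to a blinded examiner and a blinded analysis

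*Protocol article*

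**What the plan says.** All references are to the protocol article.

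- *Study design* describes the trial as "A two-armed, randomised, controlled, examiner-blinded, superiority clinical trial".
- *Randomisation, allocation, and blinding procedures* says that the assessing physiotherapist "will be unaware of randomisation and be blinded to treatment allocation" and adds: "Statistical analysis will also be conducted blinded to group allocation". It also says that "physiotherapists and participants will not be blind to treatment allocation".
- *Data collection and management* repeats that "the statistician will be blinded to the group". *Data analysis* likewise assigns the analysis to an independent, blinded person.
- The unblinding rule, in the randomisation section, reads: "The unblinding of the study will occur in case any serious adverse event occurs". The sentence goes on to give a second trigger, the end of the research, and requires for it that the data have been analysed and interpreted.
- The section on adherence, adverse events and satisfaction defines the first trigger: "Serious adverse events will include any significant disability, hospitalisation, life-threatening, and death". It sets no relatedness condition, and describes a questionnaire for events arising in the intervention period. Capture after that period is not stated.
- *Criteria for discontinuing or modifying allocated interventions* has a separate rule for stopping the study. That rule is qualified: the SAEs must make continuation harmful to participants, whether or not they are related to treatment.

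**The concern.** Unblinding after an SAE normally serves the care of one patient whose treating staff do not know the allocation. Here the treating staff and the patient already know it. The roles described as blind to allocation are the outcome examiner and those doing the analysis, so a rule that unblinds the study can remove masking only from them.

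Two things are at stake:

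- **Assessments made after the event.** Straight-leg-raise range, sciatic nerve cross-sectional area, echogenicity ratio, the neurological examination and the pressure pain thresholds used for conditioned pain modulation all depend on the examiner (*Secondary outcomes*).
- **Analysis choices.** The plan uses multiple imputation, alternative imputations and a per-protocol analysis (*Data analysis*, *Sensitivity analysis*). Knowledge of allocation can influence how these are specified.

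After a trigger, the label of an examiner-blinded trial with a blinded analysis would no longer describe what was done.

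**Working it through.** **1. Scope of the rule.** The sentence has one subject, the unblinding of the study, and two triggers: any SAE, or completion. At completion, unblinding plainly means the whole study. The same subject governs the SAE trigger, so a participant-level reading needs words that are not there. The stopping rule, by contrast, carries a qualifier (continuation must be harmful), and the unblinding rule carries none.

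**2. Who can lose blinding.**

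| Role | Status before an SAE | Can the rule change it? |
|---|---|---|
| Participants | Not blind | No |
| Treating physiotherapists | Not blind | No |
| Outcome examiner | Blind | Yes |
| Statistician | Blind | Yes |

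The sentence names no recipient of the allocation. That the last two rows are affected is inferred from the fact that no other role is described as blind to allocation.

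**3. Number at risk.** *Sample size calculation* gives 105 per group, 2 × 105 = 210. The figure reproduces: a repeated-measures ANOVA between-groups test with effect size f = 0.2, 2 groups, 3 measurements, alpha 0.05, power 90% and a correlation of 0.5 (assumed, since the article states none) needs 178. Allowing for 15% loss, 178 / 0.85 = 209.4, rounded up to 210.

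**4. Chance that the rule is triggered.** The article gives no SAE rate, so the per-participant risk p over the capture period is an assumption. With independent participants, P(at least one SAE) = 1 − (1 − p)^210, and the expected number is 210 × p.

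| Assumed p | Expected participants with an SAE | P(at least one) |
|---|---|---|
| 0.1% | 0.21 | 19% |
| 0.25% | 0.53 | 41% |
| 0.5% | 1.05 | 65% |
| 1% | 2.1 | 88% |
| 2% | 4.2 | 98.6% |

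Solving 1 − (1 − p)^210 = t for p, the chance passes 50% at p = 0.33% and 90% at p = 1.09%.

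**5. Effect of the capture window.** For an assumed annual SAE rate r and a window of w weeks, P = 1 − exp(−210 × r × w/52).

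| Assumed annual rate | 10 weeks (intervention) | 26 weeks (full follow-up) |
|---|---|---|
| 0.5% | 18% | 41% |
| 2% | 55% | 88% |
| 5% | 87% | 99.5% |

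For example, at 2% a year over 10 weeks, 210 × 0.02 × 10/52 = 0.81 and 1 − exp(−0.81) = 55%. The window matters because the article describes SAE collection only for the intervention period.

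**6. What these figures do not show.** They give the chance of at least one trigger at any time, not the share of assessments made after it. That share depends on when the event falls, and recruitment is continuous. A late event would leave most assessments already completed blind.

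**The case against.** The strongest reply is that the sentence is loosely worded and that the article commits several times to a blinded assessor and a blinded analysis. Who is told what in an emergency could be operational detail for the full protocol. This stands in part: the loss of blinding by the examiner and statistician is inferred, not stated. But the point is not a missing detail. The article states a rule, and the rule taken at its word contradicts the other commitments.

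A second reply is that allocation may be needed to judge whether SAEs make continuation harmful, and that SAEs must be reported at once to the researchers and the ethics committee. That stands as a reason for somebody to learn the allocation. It is no reason for the examiner or the statistician to learn it.

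Several stronger readings are tempting and should not be drawn:

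- **That loss of blinding is very likely.** The article gives no SAE rate. Entry is limited to ages 18–65 with several exclusions for serious illness, and risks of 0.1% to 0.25% give only 19% to 41%.
- **That the risk accrues over all 26 weeks.** Capture after the intervention is not stated.
- **That the primary results would be compromised to the same degree.** Leg pain and functional limitation are self-reported by participants who already know their group. The examiner-measured outcomes are all secondary.
- **That the examiner influences the follow-up questionnaires.** Supervision of questionnaires is described only under *Baseline assessment*, and baseline data are collected before randomisation.
- **That the whole analysis is open to influence.** The primary and secondary models are already named, which narrows the choices at risk.

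**Conclusion.** The point holds as a defect in the stated rule. One SAE in any of 210 participants, related or not, triggers unblinding of the study. The only masking left to lose is that of the examiner and the statistician, and losing it contradicts the article's own blinding statements. This conclusion rests on the wording and on the inference about recipients. It does not depend on any event rate.

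How likely the trigger is remains unknown: about 19% to 99% for assumed per-participant risks of 0.1% to 2%, and lower within that range if only the intervention period counts. The consequence falls mainly on examiner-measured secondary outcomes assessed after the event and on choices about imputation and the per-protocol set. The sentence should be corrected, but it does not by itself undermine the primary comparison.

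**What to change.** Replace the SAE part of the unblinding sentence with:

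> If a serious adverse event occurs, allocation is disclosed for that participant only, to the ethics committee or a team member not involved in assessment or analysis. The outcome examiner and statistician stay blinded until the primary analysis is complete.

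Then reconcile the new text with *Criteria for discontinuing or modifying allocated interventions*, *Data collection and management* and *Data analysis*. The stopping rule itself stays unchanged, as does immediate SAE reporting.

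The cost is one sentence and its notification as a protocol change. Treating staff already know the allocation, so no participant's care depends on the wider unblinding. If participant-level disclosure was intended all along, the same edit makes the text say so. Under the assumed risks above, the expected number of participants whose allocation is disclosed would be about 0.2 (p = 0.1%) to 4.2 (p = 2%), instead of all 210.

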### Intervention

The experimental group will receive advice to stay active associated with neural management, and the control group will receive advice to stay active alone. The experimental protocol will be performed by two trained physiotherapists, blinded to the initial assessment ([name] and [name]) and will be conducted according to the requirements Template for Intervention Description and Replication (TIDieR) [35].

